## Abstract

**Background:**

Heterogeneity in clinical manifestation and underlying neuro-biological mechanisms are major obstacles to providing personalized interventions for individuals with autism spectrum disorder (ASD). Despite various efforts to unify disparate data modalities and machine learning techniques for subclassification, replicable ASD clusters remain elusive. Our study aims to introduce a novel method, utilizing the objective behavioral biomarker of gaze patterns during joint attention, to subclassify ASD. We will assess whether behavior-based subgrouping yields clinically, genetically, and neurologically distinct ASD groups.

**Methods:**

We propose a study involving 60 individuals with ASD recruited from a specialized psychiatric clinic to perform joint attention tasks. Through the examination of gaze patterns in social contexts, we will conduct a semi-supervised clustering analysis, yielding two primary clusters: good gaze response group and poor gaze response group. Subsequent comparison will occur across these clusters, scrutinizing neuroanatomical structure and connectivity using structural as well as functional brain imaging studies, genetic predisposition through single nucleotide polymorphism data, and assorted socio-demographic and clinical information.

**Conclusions:**

The aim of the study is to investigate the discriminative properties and the validity of the joint attention-based subclassification of ASD using multi-modality data.

**Trial registration:**

Clinical trial, KCT0008530, Registered 16 June 2023, https://cris.nih.go.kr/cris/index/index.do.

**Supplementary Information:**

The online version contains supplementary material available at 10.1186/s12888-023-04978-4.

## Background

The early onset [1], diverse clinical and neurobiological features [2–4], and rising prevalence of autism spectrum disorder (ASD) [5, 6] highlight the urgent need and associated challenges for its subclassification. Recent advancements in genomics [7–9] and neurobiology [10–13] underscore the disorder’s complexity, revealing various etiological pathways. This wide spectrum of ASD symptoms poses both a hurdle and incentive for subclassification. Subclassification methodologies are distinguished by the type of data analyzed and the algorithms used for grouping [12]. The data can be behavior-based or biology-based, each indirectly indicating variations in the other [14, 15]. Moreover, subclassification algorithms range from supervised and unsupervised to hybrid models, each using univariate or multivariate statistics, with their respective pros and cons [16].

### Genomic subclassification of ASD

Genetic factors are the primary risk contributors to ASD, encompassing a range of both rare and common genetic variants. This includes rare de novo mutations, copy number variants, protein-truncating single nucleotide polymorphisms (SNPs), indels, and even non-coding de novo mutations in chromatin interactions [17, 18]. Previous studies have linked these genetic elements to the wide-ranging clinical manifestations of ASD. The genetic origins of ASD are complex and multifactorial; however, our grasp of how these genetic elements functionally influence ASD is still limited. Additionally, the way these genetic factors interact with each other and non-genetic factors to shape risk remains uncertain. However, considering the enormous number of variants implicated in ASD, coupling these genetic data with other types of data obtained through different modalities may help us discern specific genetic vulnerabilities and their corresponding functional consequences in ASD [19].

### Neuro-subclassification of ASD

A few studies have explored neuroanatomical differences between individuals with ASD and neurotypical individuals, as well as within the ASD group itself [11–13, 20]. A significant portion of this research has been conducted using the Autism Brain Imaging Data Exchange (ABIDE) dataset, an open-source compilation of brain imaging data from ASD and neurotypical individuals [21, 22]. Using this resource, Hong et al. identified three distinct ASD subclasses with varying clinical outcomes, based on cortical thickness, intensity contrast, surface area, and geodesic distance [20]. Choi et al., applying an unsupervised clustering approach to ABIDE’s resting state fMRI (rsfMRI) data and utilizing ‘connectome-based gradient’ and ‘functional random forest’ methodologies, were able to differentiate various forms of ASD [12]. However, their results lacked complete replicability as the clinical scores of the subgroups identified through cluster analysis in a follow-up dataset deviated from those in the original dataset. Additionally, these ASD clusters failed to show significant differences in neural connectivity [12, 20]. These outcomes imply that purely unsupervised clustering using intricate data like fMRI might not yield clinically meaningful ASD subtypes.

### Clinical score-driven subclassification of ASD

A research team adopted a top-down approach in their pursuit of developing a new ASD subclassification method, using a clinical-score based clustering method and multimodality data [23]. While this approach allowed for the identification of distinct ASD subgroups based on balance between social-communicative and restricted repetitive behaviors – the two main symptom domains of ASD), these ASD subgroups showed no evident differences in neural circuitry and genetic components [23].

### Limitations of previous studies

Previous attempts at cluster analysis using unsupervised learning on intricate data such as fMRI did not yield consistent or replicable subclassifications; even with identical experimental parameters, the replication dataset did not reproduce the same ASD subgroups as the original discovery dataset [11–13]. Without any labels to guide the clustering, individuals were grouped into distinct subclusters based on non-linear data patterns that lacked clinical significance. Meanwhile, studies using supervised learning methods for cluster analysis also fell short, failing to identify subgroups with unique clinical phenotypes and neurobiological mechanisms [23]. It is worth noting that these studies used human-rated autism-related scale sub-scores as labels for supervised learning. Although these scores are clinically valid and frequently used, they may not adequately capture objective and qualitative differences in ASD phenotypes.

### Possible objective behavioral biomarker for subclassification of ASD

Joint attention, as indicated by prior research, may serve as an objective behavioral biomarker for ASD subclassification [24, 25]. This term refers to the sharing of attentional focus with others on objects or events and is believed to aid social learning [26, 27]. We have established a digitized method to assess joint attention, implementing a novel protocol to prompt three types of joint attention - initiation of joint attention (IJA), low-level and high-level response to joint attention (RJA_low_ and RJA_high_) - as defined in the Early Social Communication Scales (ESCS) [28]. This method uses video-recorded task-related behaviors [26, 27], which are then utilized to train a deep learning model to identify ASD and evaluate its symptom severity [25].

Identifying the most affected level—biological, neural, or behavioral—in an individual with Autism Spectrum Disorder (ASD) to determine the suitable targeted intervention is a significant challenge. To address this, we have initiated the development of the Yonsei-Seoul Multi-modal Subclassification (YSMS) protocol, which was designed to streamline data collection from newly diagnosed ASD patients. Specifically, the focus is on the patterns of joint attention gaze demonstrated during behavioral tasks, with the aim to discern whether these patterns can differentiate various ASD subtypes, each unique in their biological and neurological attributes. We intend to implement a pilot version of this protocol in an exploratory study involving 60 individuals diagnosed with ASD from June 2023 to May 2024 to compare objective behavioral biomarker-based ASD subgroups using multimodality data. Such endeavor is expected to drive the creation of a novel ASD subclassification system, considering each individual’s biological, neural, and behavioral characteristics.

## Methods

### Recruitment

We have designed a single center, prospective, non-randomized experimental study, where individuals with ASD diagnosis will be recruited from June 2023 – May 2024. A group of 60 ASD individuals will be recruited from outpatient clinic at the Child and Adolescent Psychiatry Division of Seoul National University Hospital (SNUH). Enrollment criteria are: (1) age of 30 ~ 71 months, (2) children diagnosed with ASD by a psychiatrist and confirmed by Autism Diagnostic Observation Schedule II (ADOS2). Exclusion criteria are: (1) history of organic brain injury, (2) having visual or auditory deficit, (3) having neurological (motor/musculoskeletal) conditions, (4) history of adverse reaction to sedation anesthesia. A schematic showing the flow of patients is depicted in Fig. 1.

**Fig. 1 Fig1:**
[figure not shown]
Recruitment and Overall Study Schema

### Multi-modal Data Collection – different types of data

#### Socio-demographics and family history

We gather information about each participant’s socio-demographics and family history to consider for environmental risk factors that may have contributed to different social gaze patterns during joint attention tasks. Patient information such as sex and age at time of assessment will be gathered. Family information such as parental age, parental education level as well as socio-economic status will be gathered from parent interviews. Moreover, number of siblings as well as neuropsychiatric history of siblings will also be obtained.

#### Clinical assessments - neuropsychiatric tests

The diagnosis of ASD is confirmed using ADOS-2, the gold standard diagnostic tool for ASD diagnosis [29]. Autistic tendencies are measured using the Korean versions of the Social Responsiveness Scale (K-SRS) as well as Social Communication Questionnaire (K-SCQ) [30]. The Social Responsiveness Scale (SRS) is a 65-item questionnaire, scored from zero to three based on the frequency of the described behavior, that evaluates the social interactions of children over the past six months, with higher scores indicating lower social capability [30]. The SCQ is a 40-item screening instrument that is based on Autism Diagnostic Interview-Revised (ADI-R), a tool for more in-depth assessment of ASD symptoms, and selects key items that deviate from normal development [30, 31].

Child behavioral problems will be checked with Child Behavior Checklist (CBCL) as well as Vineland Adaptive Behavior Scale (VABS) [32]. The child’s motor functions will be assessed through Developmental Coordination Disorder Questionnaire (DCDQ) [32]. To assess the cognitive levels of participants, the Korean Wechsler Preschool and Primary Scale of Intelligence–Fourth Edition (K-WPPSI-IV) will be used [33].

#### Joint attention tasks and Video Data

We will conduct three types of joint attention tasks in the order of initiation of joint attention, low-level response to joint attention, and high-level response to joint attention according to the Yonsei Seoul Multi-modal Subclassification (YSMS) Joint Attention Task Standard Operating Procedure. Development and validation of AI model trained on video data collected using this protocol has been published elsewhere [24, 25]. Supplementary Fig. 1 shows setup for joint attention experiments based on our proposed protocol. Initiation of joint attention task requires use of only toy 1, while low level response to joint attention task requiring use of toy 1 and toy 2 (distraction) and high-level response to joint attention task requiring use of four picture prompts.

#### Video (RGB or RGB-D)-based Gaze Estimation during Joint attention situations

Following the YSMS Social Gaze-Based Clustering Standard Operating Procedure, we will gather joint attention videoclips for purpose of determining gaze patterns of each participant during joint attention tasks. Joint attention tasks were slightly modified from previous study [24, 25], whereby picture prompts are placed on the same plane as the examiner and toy objects so that all gaze points will fall on the same imaginary vertical hyperplane parallel to the participant’s head/eyes, as shown in Supplementary Fig. 8. With such videorecording set-up, RGB-D information (if using RGB-D device) as well as head’s yaw, pitch, and roll may be computed via computer vision techniques such as algorithm for estimating 3D position of the head and face-tracker [34]. Head position and orientation is tracked through the frame sequence and at every time point this information is stored for later analyzing different patterns of social (joint attention situations) gaze among participants.

#### Magnetic resonance imaging Acquisition and Processing

We use magnetic resonance imaging (MRI) to study differences in brain structure [35], function, and connectivity [36–38]. These methods are important for determining whether different clusters or subgroups of ASD based on social gaze patterns differ at systems-level, providing the underlying neurological mechanisms of different types of ASD. We will be gathering all MRI data from a single center—SNUH.

#### Structural MRI (sMRI) and Diffusion Tensor Imaging (DTI)

MRI scans are acquired on 3T scanners from Siemens (https://www.siemens-healthineers.com/). We will carry out several procedures to optimize structural and functional sequences for the best Siemens-specific options and to address challenges related to standardization and quality assurance of image-acquisition.

Global descriptors of brain anatomy can be elucidated through measures of total grey and white matter volume [35]. Alongside these metrics, we will probe into distinctions in cortical thickness, intensity contrast, geodesic distance, and cortical surface areas. These anatomical indices possess unique genetic determinants, phylogeny, and developmental trajectories [35, 36]. Furthermore, we will calculate structural connectivity indices utilizing both structural MRI scans and Diffusion Tensor Imaging (DTI). Variations in intrinsic grey matter connectivity can be inferred by examining the disparities in both local and global wiring costs [37]. Concurrently, distinctions in short and long-range white matter tracts can be evaluated using tractography analysis of particular pathways [38].

### Resting state functional magnetic resonance imaging (rsfMRI)

Standard gradient-echo echo planar imaging paradigm will be utilized for the acquisition of resting state fMRI scans [39]. We will carry out several procedures to find optimal parameters such as field of view, repetition time, echo time, flip angle, etc. During the resting state scan, participants will be sedated with their eyes closed. The Configurable Pipeline for the Analysis of Connectomes (CPAC, http://fcp-indi.github.com) preprocessing pipeline will be employed for fMRI data processing to remove non-neural noise, such as motion artifacts, from the BOLD-signal [12, 20]. Multiple functional networks have been identified that are characterized by coherent patterns of intrinsic activity between ‘nodes’ that resemble patterns of activity that are engaged during specific cognitive functions [12]. We aim to identify whether social gaze-based subgroups differ in (hyper/hypo-) connectivity within and across these networks [10, 11, 13].

#### Whole genome sequencing (WGS)

We acquire blood samples from the participant for genomic analyses—we specifically wish to identify all variants associated with ASD and calculate polygenic risk scores for each participant. These methods are important for determining whether different clusters or subgroups of ASD based on social gaze patterns differ at the genetic, blueprint-level; ASD individuals may show varying social gaze patterns based on their entire mutation profile.

Collection and Processing of Peripheral Whole Blood Samples: Each participant will contribute a 3ml sample of peripheral whole blood. These samples will be subjected to genomic DNA extraction and whole genome sequencing, performed with the NextSeq 550Dx System (Illumina, San Diego, CA, USA). The procedure for whole genome sequencing will adhere to an industry standard quality-controlled sequence analysis pipeline and utilize a current reference sequence for the purposes of mapping and variant calling [40].

Identification of single nucleotide polymorphisms (SNPs) and insertions and deletions (indels) will be conducted with HaplotypeCaller and MuTect2 from the GATK package (3.8-0, https://github.com/broadinstitute/gatk/releases), as well as with VarScan2 (2.4.0, https://github.com/dkoboldt/varscan/releases). A variety of databases will be used for the analysis and annotation of variants, including but not limited to, the Online Mendelian Inheritance in Man (OMIM), the Human Gene Mutation Database (HGMD), Clinvar, dbSNP, 1000 Genomes, the Exome Aggregation Consortium (ExAC), the Exome Sequencing Project (ESP), the Korean Reference Genome Database (KRGDB), Autism Speaks MSSNG resource, and the Simons Simplex Collection (SSC). Variants will be classified following the standards and guidelines set forth by the American College of Medical Genetics (ACMG) [41]. Following annotation, the sequencing data will undergo additional processing to compute polygenic risk scores for ASD of the top SNPs after thresholding the SNP component [42]. Such computation aims to aid in differentiating between individuals with Autism Spectrum Disorder (ASD) based on their distinct genetic susceptibility or polygenic risk variability.

The different types of data for comparison between subgroups of ASD are listed in Table 1.

**Table 1 Tab1:** Different types of data acquired in proposed study

Data Types	Case Report Form	Neuro-psychiatric Tests	Brain Imaging	Whole Genome Sequencing	Video
Contents	- Age/sex - Parental age - Parental socio-economic status & education - Number of siblings - ASD in siblings - Diagnosis - Comorbidities	- WPPSI - ADOS2 - SRS - SCQ - CBCL - VABS - DCDQ	- SIEMENS Magnetom Trio 3.0T - sMRI - DTI - rsfMRI - DICOM file	- Source: whole blood - GATK - Variant call format file (annotation)	- RGB or RGB-D camera - Joint attention tasks for ~ 5 min - RGB (color), depth files

## Considerations related to the statistical analysis

### Statistical models and analyses

#### Social Gaze-based semi-supervised clustering analysis

From our previous study, we explored certain relationships between individuals with ASD and clinical scores as well as their performance on joint attention tasks, namely initiation of joint attention and response to joint attention [24, 25]. Such analyses revealed that variables that explain for the variance within group of ASD individuals is their performance in joint attention tasks. Hence forth, we will use join attention success rate for the three different joint attention tasks and perform principal component analysis followed by semi-supervised k-means clustering analysis [43] - using good and poor gaze response head-pose values as labels - to obtain two ASD subgroups, one with decreased joint attention and the other with intact joint attention. An alternative method would be to use a range of threshold value *k* to divide the group of ASD individuals in two sub-groups where one group shows relatively better joint attention abilities.

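### Both grouping methods fix two groups in advance and call one 'intact', so neither forming the groups nor a positive external comparison can show discrete ASD subtypes

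*Protocol article*

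**What the plan says.** All references are to the protocol article.

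- **Number of groups.** The Methods part of the Abstract gives the clustering result before any data exist: "yielding two primary clusters: good gaze response group and poor gaze response group". The section on social gaze-based semi-supervised clustering takes success rates on the three joint attention tasks, applies principal component analysis and then semi-supervised k-means. The stated purpose is "to obtain two ASD subgroups, one with decreased joint attention and the other with intact joint attention". The supervision itself comes from two classes, "using good and poor gaze response head-pose values as labels".
- **Alternative.** The same section offers a threshold approach "to divide the group of ASD individuals in two sub-groups where one group shows relatively better joint attention abilities".
- **Aim.** The Abstract's Conclusions state it as to "investigate the discriminative properties and the validity of the joint attention-based subclassification of ASD".
- **Criticism of earlier work.** Under Limitations of previous studies, unsupervised clustering is faulted because "the replication dataset did not reproduce the same ASD subgroups as the original discovery dataset".
- **Who is enrolled.** Recruitment: "A group of 60 ASD individuals will be recruited from outpatient clinic". No neurotypical group, norm or cut-off for intact joint attention is given. The Outcome section softens the label to mostly intact, but its table heading returns to intact.
- **What follows.** The two groups are compared on clinical, imaging and gaze measures, and the Outcome section adds genetics. The comparison section mentions validation measures once, without naming them or giving a criterion.

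**The concern.** k-means with k = 2 partitions whatever it is given. Seeding it with two classes, good and poor, reinforces this, and the threshold alternative is a dichotomy by construction. Under neither route can the grouping step return one group or three. Yet the sample size section leans on an earlier cohort of 45 in which three severity subclasses were found.

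This matters because the aim is the validity of the subclassification. If joint attention varies along one dimension in these children, the plan as described would still produce two well-separated groups, and nothing in it would point to the simpler account. The background section expects the study to drive a new subclassification system, so the distinction between types and a dimension is central.

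The label is a separate problem. A split made within a sample of children with ASD ranks them against each other. It cannot show that the upper group's joint attention is intact, which is a statement about a population that is not measured.

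**Working it through.** **Inputs from the article:** n = 60; three success rates; principal component analysis, then k-means; two groups; p < 0.05.

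**Assumptions, because the article gives no values:** normally distributed scores from a single continuous factor with no subgroups; shared variance between tasks of 0.3, 0.5 or 0.7; a range of correlations with external measures. The head-pose labels could not be simulated, so ordinary 2-means stands in for the semi-supervised version.

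**Step 1: does one continuum yield two separated groups?** A hand calculation comes first. Split a standard normal score at its mean:
- group means are ±√(2/π) = ±0.798, a difference of 1.596;
- within-group SD is √(1 − 2/π) = 0.603;
- standardised gap is 1.596 / 0.603 = 2.65.

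Simulation agrees. In 1,000 data sets per setting at n = 60, two groups were returned every time, with a median smaller group of 26 to 27. The standardised gap was about 2.7 on the first component. On the mean joint-attention score it was 2.6 to 3.1, the upper end coming from six-trial success rates. The groups differed on joint attention at p < 0.05 in 99.9% to 100% of data sets. A large, significant difference in joint attention is thus the expected result when there are no subgroups.

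**Step 2: can the external comparisons settle it?** Share of continuum-only data sets (n = 60) in which an external measure differed between the groups at p < 0.05:

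| Assumed correlation | With the underlying factor | With the first-component score |
|---|---|---|
| 0 | 4% to 5% | 3% to 6% |
| 0.3 | 30% to 41% | 47% to 49% |
| 0.5 | 65% to 88% | up to 94% |

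The columns differ because the observed score measures the factor with error. The first row shows that the external comparison can fail. The others show that it can succeed with no discrete types present.

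**Step 3: what does the split cost under a continuum?** Dichotomising a normal score at its mean multiplies a correlation by 0.798, so 0.3 becomes 0.239. Approximate power at n = 60 is Φ(atanh(r) × √57 − 1.96):
- continuous score: 0.3095 × 7.55 − 1.96 = 0.377, power about 65%;
- split: 0.2437 × 7.55 − 1.96 = −0.12, power about 45%.

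Simulation gave 64% to 69% for the continuous score and 47% to 49% for the split.

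**Step 4: could a formal one-cluster test decide?** Only for wide separation. Across separate simulations with somewhat different settings, a parametric bootstrap test of one cluster rejected as follows:

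| True separation | Rejection rate |
|---|---|
| 0 SD | 0 |
| 2 SD | 0 to 0.08 |
| 3 SD | 0.31 to 0.63 |
| 4 SD | 0.97 to 0.99 |

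The test is conservative: a test of exact 5% size would give no rejection in 150 null data sets with probability 0.95^150, about 0.0005. Non-rejection at n = 60 therefore says little about groups less than about 3 to 4 SD apart.

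**The case against.** **The external comparisons can be null.** A reader might infer that the whole subclassification cannot fail. The documents do not support that. The Abstract asks whether the groups are clinically, genetically and neurologically distinct, and step 2 shows that this can come out negative. What stands is narrower: a positive answer does not separate types from a continuum.

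**The article is condensed.** A reader might also infer that the study never tests cluster structure. That cannot be established. The article mentions unnamed validation measures, a clustering operating procedure and a cited method, and a fuller document may specify checks. The point therefore rests on what the article fixes, namely two groups under either method and the word intact. It says only that no check is described.

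**Two groups may be deliberate.** The authors criticise purely unsupervised clustering for clinically meaningless groups and choose label-guided grouping in response. The alternative claims only a split "where one group shows relatively better joint attention abilities", over a range of thresholds, and the study is a pilot and exploratory. This is fair. A pragmatic split is legitimate if it is described as one, but it does not support intact or a claim of distinct types.

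**The simulation is not the planned procedure.** That is correct, so its exact figures are illustrative. The main conclusion does not depend on them, because the number of groups is set by the method.

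**A hard rule would err the other way.** Barring any subtype claim whenever a one-cluster test fails to reject would miss true groups 2 SD apart in 92% to 100% of samples (step 4). This objection stands, and the fix avoids such a rule.

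**Conclusion.** The point holds in this form. The article fixes two groups under both methods and describes no check against a single continuum, so obtaining two separated groups is not evidence of two types. With no subgroups, a gap of about 2.7 SD is expected. The external comparisons can refute an association, but a positive result would also arise from a continuum, in 47% to 94% of data sets at correlations of 0.3 to 0.5 with the score. 'Intact' is unsupported because the sample has no reference group and no norm.

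The sizes rest on normal scores, the assumed correlations and unseeded 2-means. That two groups are always formed, and that the label lacks a reference, does not. This should be fixed, but it does not undermine the study: the design is exploratory, data collection is unaffected, and the remedy lies in wording and analysis.

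**What to change.** 1. In the clustering and Outcome sections, including the outcome table, rename the groups higher and lower joint attention within this ASD sample, and drop 'intact'.
2. Alongside each two-group comparison, analyse the joint-attention score (first principal component) as a continuous predictor of the clinical, imaging and genetic measures.
3. Report descriptively the fit for k = 1 to 4, bootstrap cluster stability, and agreement between the seeded and unseeded solutions. Set no fixed stability cut-off, since the documents give no basis for one.
4. Claim discrete subtypes only if these checks support them. Otherwise describe the groups as a split of a dimension, and state that at n = 60 failure to reject one cluster is not proof of a continuum, because the test has little power below about 3 to 4 SD separation.

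The cost is some wording and a little more analysis of data already planned, with no extra participants or visits. The conclusion may be more cautious. The changes should be settled before the data are clustered.
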